## Methods

### Participant Selection

The sample size was calculated as 18 individuals for each group using the G*Power program (version 3.1.9.4; Heinrich Heine University) with 90% power and .05 type 1 error using the medio-lateral swing effect size value as reference in the balance assessment in the study by Tat et al [19]. Considering that there might be individuals who would not complete the study, a total of 63 participants, that is, 21 individuals for each group, will be included.

The inclusion criteria of the participants in this study were as follows: (1) diagnosed with hemophilia A and hemophilia B, (2) have a blood factor level below 5%, (3) is 13-25 years of age, (4) have a history of bleeding in the lower extremities, (5) have a target joint, (6) have a total lower extremity Hemophilia Joint Health Score ≥3, and (7) is receiving prophylaxis (factor support to prevent bleeding). The exclusion criteria were as follows: (1) individuals having undergone lower extremity surgery in the last 6 months, (2) having BMI>30 kg/m^2^, (3) having an inhibitor, (4) using a walking aid, and (5) being involved in any physiotherapy or exercise program in the last 6 months.

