### Study Design

This study has been registered with Clinical Trials.gov (NCT05879549). It is a 3-arm, parallel-group, single-blinded randomized controlled trial. This trial has been reported according to CONSORT (Consolidated Standards of Reporting Trials) guidelines (Multimedia Appendix 2) and the SPIRIT (Standard Protocol Items: Recommendations for Interventional Trials) checklist (Multimedia Appendix 3). This study will be performed in Istanbul University-Cerrahpaşa Laboratory. A permit has been obtained from the institution. The demographic characteristics of the participants (age, height, weight, diseases, etc) will be recorded. Participants will be divided into 3 groups using a simple randomization method according to the order of arrival (1:1:1) with a web-based randomizer. Participants do not know the exercise group that they will be included in nor will they know the differences between the exercises. The flowchart of this study is shown in Figure 1.

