### Statistical Analysis

Data will be statically analyzed using SPSS (version 25.0; IBM Corp). Normality tests (visual and analytical) will be applied. Descriptive statistics will be presented as mean (SD) or frequency (percentage). The Shapiro-Wilk test will be used to assess the normality of data distribution. For normally distributed data, a one-way analysis of variance test will be applied for between-group comparisons, and a 2-sided paired sample *t* test will be used for within-group changes. For nonnormally distributed data, the Kruskal-Wallis test will be used for between-group comparisons, and the Wilcoxon test will be applied for within-group changes. In cases where between-group comparisons of normally distributed data show significant results, Tukey or Bonferroni corrections will be used as post hoc analyses to identify the source of the differences. For nonnormalized distributed data, Mann-Whitney *U* tests will be conducted for between-group comparisons. A *P* value <.05 will be considered statistically significant for all analyses.

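### No Kruskal-Wallis gate or correction is written for the Mann-Whitney pairs, though the ANOVA route has both: family-wise error is about 12% or about 5% per outcome, depending on the reading

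*Protocol article*

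**What the plan says.** The Study Design section states: "It is a 3-arm, parallel-group, single-blinded randomized controlled trial". Each outcome therefore has three pairs of arms to compare.

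The Statistical Analysis section splits outcomes by normality: "The Shapiro-Wilk test will be used to assess the normality of data distribution". The same section also mentions visual checks. Normal outcomes go to one-way ANOVA and the rest to Kruskal-Wallis.

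The pairwise rules then differ:

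- **Normal outcomes:** "In cases where between-group comparisons of normally distributed data show significant results, Tukey or Bonferroni corrections will be used as post hoc analyses". This contains a condition (a significant overall result) and a correction, though it does not say what decides between the two corrections.
- **Nonnormal outcomes:** for Mann-Whitney the text is "tests will be conducted for between-group comparisons. A". No condition and no correction is attached.

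One threshold covers everything: a P "value <.05 will be considered statistically significant for all analyses".

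**The concern.** The condition and the correction are both expressly limited to normally distributed data. The next sentence, on nonnormal data, has neither, and the blanket .05 threshold follows at once. An analyst who follows the text as written would run three Mann-Whitney tests per outcome, each at .05, whatever Kruskal-Wallis shows.

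The family-wise error for the pairwise claims on an outcome would then depend on how its normality check came out. Each single Mann-Whitney test would still be at about .05; it is the chance of any false claim among the three that changes. The pairwise claims include the head-to-head comparison of the two exercise programmes, which is the stated purpose of the trial.

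**Working it through.** **Inputs**

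- Arms: 3, so 3 pairs per outcome (Study Design).
- Level: .05 for each test (Statistical Analysis).
- Sidedness: written only for the within-group test ("a 2-sided paired sample"); two-sided is assumed for Mann-Whitney.
- Size: "The sample size was calculated as 18 individuals for each group" (Participant Selection), with 21 per group enrolled to allow for losses. Both are used.

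The article states no family-wise error rate, so there is none to reproduce. Its sample size cannot be reproduced either, because no numerical effect size is given. Here it serves only to fix the number per arm.

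**Step 1. Three Mann-Whitney tests at .05, no gate, no correction**

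- Bound if the three tests were independent: 1 − 0.95³ = 1 − 0.857 = 14.3%.
- The pairs share arms, so the true figure is lower. In large samples it is the chance that the studentized range of 3 groups exceeds 1.96 × √2 = 2.77, which is 12.2%.
- Simulation with three equal arms (100,000 runs per setting):

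| Per arm | Normal data | Lognormal data |
|---|---|---|
| 18 | 12.6% | 12.7% |
| 21 | 12.0% | 11.9% |

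A separate check gave 11.9% at 18 and 12.2% at 21. About 12% to 12.6% is a fair summary.

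**Step 2. The same tests, only after a significant Kruskal-Wallis test**

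- All arms equal: 4.9% at 18 per arm and 4.8% at 21.
- One arm truly different by 0.5 to 3 SD, at 18 per arm: the one remaining true null is falsely rejected in 3.9% to 5.1% of runs.

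This is expected with exactly three arms. If all are equal, the gate limits the error. If one differs, only one pair is still a true null, and it is tested at .05. The argument does not carry over to four or more arms.

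**Step 3. A correction in place of the gate**

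Ungated Mann-Whitney at .05/3 = .0167 gives 4.2% at 18 per arm and 4.1% at 21. Holm starts at the same .0167, so with all arms equal its rate is identical.

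**Step 4. The ANOVA route at 18 per arm, all arms equal**

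| Rule | Family-wise error |
|---|---|
| ANOVA gate, pairs unadjusted | 5.0% |
| Tukey alone | 5.0% |
| ANOVA gate plus Tukey | 4.5% |
| ANOVA gate plus Bonferroni | 4.2% |

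Every row holds 5%. The last two, which are what the article describes, are slightly conservative.

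**Step 5. What that conservatism costs**

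An effect size has to be assumed. With 18 per group, 90% power and .05, a two-group t test implies 1.11 SD if two-sided and 1.00 SD if one-sided. (A three-group F test implies f = 0.499.) With one arm differing from two that are alike, power for a truly different pair is:

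| Assumed difference | Gate plus Tukey or Bonferroni | Gate, unadjusted pairs |
|---|---|---|
| 1.11 SD | 80% to 82% | 88% |
| 1.00 SD | 70% to 72% | 80% |

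The gain depends on the pattern of means and on the assumed effect.

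**The case against.** The strongest reply is that the missing gate is inferred from silence. Kruskal-Wallis is named for the same data and would have little purpose if Mann-Whitney ran regardless of it. The Mann-Whitney sentence also comes directly after the one on post hoc tests, so reading it as the nonparametric post hoc step is at least as natural. On that reading the rate is about 5% and nothing is inflated. This stands: a reader might infer that the trial will run at 12% error on nonnormal outcomes, and the article does not establish that.

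A reader might also compound the 12% over the four primary outcomes. The article does not support that. It would require all four to be nonnormal and all to be tested ungated, and it would mix in the separate question of having several primary outcomes.

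Third, a correction after a significant ANOVA is valid. It may be called redundant with three arms, but it is not an error.

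Finally, this is a condensed article, and a fuller analysis plan may state the rule. That would excuse plain silence. It does not fully answer the point here, because the article does write the pairwise rule: it ties the condition and correction to one type of data, omits both for the other, and applies one threshold to all.

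**Conclusion.** The point holds as a conditional one. The article does not fix the pairwise rule for nonnormal outcomes. The two available readings give a family-wise error of about 12% to 12.6%, or about 5%, per outcome. These figures assume two-sided tests, 18 to 21 evaluable per arm and no true differences. They barely change between normal and lognormal data.

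The open choice between Tukey and Bonferroni is a smaller looseness of the same kind, since both keep the error below 5%. The power gain from dropping the second correction on the ANOVA route is an optional improvement, and its size rests on assumed effects of 1.0 to 1.11 SD that the article does not state.

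**What to change.** State one pairwise rule for both routes. Either of these would do:

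1. Compare pairs only if the three-arm test (ANOVA or Kruskal-Wallis, as applicable) is significant at .05, then test each pair at .05. With three arms this holds about 5%.
2. Apply Holm to the three pairwise P values, on both routes.

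In either case, replace the choice between Tukey and Bonferroni with a single named method. The outcome of the normality check would then no longer alter the multiplicity rule.

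Option 1 also brings the power gain on normal outcomes described above. Its small downside is that unadjusted pairs do not come with simultaneous confidence intervals. If those are wanted, that is a reason to keep one named correction.

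The cost is a sentence or two in the Statistical Analysis section, with no extra data or staff. The Results section says analysis begins only once all enrolled participants have finished treatment, so the change can be recorded beforehand.

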## Results

This research received funding from the Turkish Scientific and Technological Research Institution as of September 1, 2023. From this date, cases began to be incorporated into the study. By April 2025, a total of 34 participants had completed the treatment phase. Once all enrolled participants have finished their treatment, data analysis will commence. The anticipated completion date for this study is May 2025.

## Discussion

This study will investigate the effects of 2 different exercise approaches on functional parameters in people with hemophilia. In this study, the effects of exercise protocols on parameters such as postural sway, walking speed, and joint health will be evaluated. The predicted main findings of this study suggest that both exercise approaches may positively affect functional parameters such as postural sway, walking speed, and joint health in individuals with hemophilia, with anticipated improvements in balance and gait.

Recurrent bleeding in the lower extremities of people with hemophilia may cause changes in gait. Fouasson-Chailloux et al [28] observed that patients with moderate hemophilia may have impairments in gait parameters if their joint health scores are poor [28]. Joint movement limitations in people with hemophilia may occur due to movement restrictions and pain sensation, and this may lead to decreased pressure in the forefoot center and shorter step length [28]. Fukuchi et al [29] reported that people with hemophilia walked with less range of motion in the hips and ankles compared to their healthy peers. In addition, a decrease in gait speed and step length and an increase in double support and swing phase duration were observed in patients with moderate or severe hemophilia [30]. Changes in the walking patterns of boys with hemophilia are associated with changes in physical function performance [15]. Deniz et al [31] reported that an 8-week structured exercise program can improve the kinematic parameters of walking. For these reasons, the effect of exercise programs on walking will be investigated in our study, and for this purpose, changes in walking speed and kinematic parameters will be evaluated using the Kinovea software (Joan Charmant, open source).

Recurrent bleeding is the major factor leading to hemophiliac arthropathy. Lower extremity arthropathies may cause balance problems. A previous study [19] where static posture was evaluated using Biodex similar to our study showed that medio-lateral oscillations increased in people with hemophilia. These changes were found to be associated with the clinical scores of the lower extremity joints. That study emphasized the importance of balance assessment and suggested that exercises to enhance medio-lateral stability should be incorporated into rehabilitation programs. Although lower extremity arthropathies may affect balance scores, worse balance scores have been reported in patients with and without hemophilic arthropathy compared to healthy individuals. For this reason, we incorporated methods from the literature known to positively impact balance parameters into our study.

Exercise training is one of the most commonly recommended methods to prevent and treat musculoskeletal problems that may develop in patients with hereditary bleeding disorders [15]. Traditionally, the most commonly used exercise types are aerobic exercises, strengthening exercises, aquatic exercises, and combined training. In our study, the effectiveness of customized exercise programs will be compared differently from that in existing literature. Chronic synovitis, cartilage damage, and subchondral bone damage due to recurrent joint bleeding in people with hemophilia may decrease proprioceptive information [32]. For this reason, one of the exercise groups that we planned was based on proprioception. The effect of progressively developed sensorimotor exercises on balance and gait parameters will be revealed.

Gönen et al [33] performed different exercise trainings for 21 patients for 12 weeks in people with hemophilia: 7 patients were included in the closed kinetic chain exercise training group, 7 in the conventional exercise group, and 7 in the control group. They concluded that closed kinetic chain exercise training was superior in proprioception and physical activity compared to conventional exercises for people with hemophilia A [33]. In our study, we aim to investigate the effects of closed kinetic chain exercises on balance and gait parameters. Additionally, by the end of the study, we will compare the outcomes of proprioceptive exercise training and those of closed kinetic chain exercises. This comparison will contribute to developing optimal exercise training programs for people with hemophilia.

Bleeding episodes induced by exercise in people with hemophilia have been reported as rare adverse events [15]. In our study, to prevent any bleeding during exercises, the exercises were scheduled on the days when patients received their factor replacement therapy.

A limitation of this study is the lack of long-term follow-up, which is particularly relevant, given that hemophilia is a chronic condition that predisposes individuals to ongoing musculoskeletal system challenges. The absence of extended outcome assessments limits the ability to evaluate the sustained effects of the exercise interventions on balance, gait, and joint health over time.

Our study will contribute to the literature as the first study comparing the protocols of closed kinetic chain exercises and proprioceptive exercises in people with hemophilia. We expect our study to be a pioneer in the future, especially in protocols that contribute to the improvement of daily life activities such as balance and walking, which are affected by bleeding.

## Appendix

Multimedia Appendix 1 Peer-reviewer report from the Turkish Scientific and Technological Research Institution.

Multimedia Appendix 2 CONSORT-EHEALTH (Consolidated Standards of Reporting Trials of Electronic and Mobile Health Applications and Online Telehealth) checklist (version 1.6.1).

Multimedia Appendix 3 SPIRIT (Standard Protocol Items: Recommendations for Interventional Trials) checklist.

## Abbreviations

6MWD: 6-minute walk distance
CONSORT: Consolidated Standards of Reporting Trials
SPIRIT: Standard Protocol Items: Recommendations for Interventional Trials
